#### Delivery

Co-design of intervention delivery with the implementation partner prioritized remote delivery to ensure equitable accessibility to the intervention across Australia by using a dedicated web-based digital platform, supported by health coaching (delivered via phone or videoconference), with ongoing text message support (Figure 1).

**Figure 1 figure1:**
[figure not shown]
OptimalMe program design and delivery.

#### Platform

The secure web-based platform can be accessed via desktop and mobile apps. The platform contains preconception, pregnancy, and postpartum modules. Participants are provided access to the preconception module at the outset from the dashboard (Figure 2). The pregnancy module is accessible to participants when they update their personal profile on the dashboard (pregnancy status and estimated due date). In addition to the 3 modules, the dashboard contains an interactive BMI (and gestational weight gain, if pregnancy is reported) calculator, a checklist, and activities to review behavioral action plans.

All modules have a similar format—each has a health information (education) section and a healthy lifestyle behavior change (self-management) section. The health information section contains health, medical, and screening information and the healthy lifestyle section contains diet and physical activity recommendations, as well as an interactive behavior change section. Health, medical, and screening information are presented as a suite of fact sheets specific to each reproductive phase (Multimedia Appendix 2). Information provided is based on the Royal Australian College of General Practitioners Red Book [29], Australian Government Clinical Practice Guidelines for Pregnancy [30], and our formative research [33,34]. A series of health screening questions at module commencement based on these guidelines will inform the presentation of fact sheets according to relevance. For example, preconception participants will be asked when their last cervical screen was completed. If a participant indicates a cervical screen outside of a guideline-specified timeframe, the relevant cervical screening fact sheet will be presented under *Essential information* at the top of the screen. Conversely, if a participant indicates a cervical screen within a guideline-specified timeframe, the fact sheet will be presented under *Other recommended reading*. This design feature ensures that participants are directed to the information that is most relevant to their health needs (based on their responses to screening questions) while minimizing the burden of information, which has previously been identified as a barrier to receiving health information [31].

Fact sheets have a similar structure—each fact sheet has 3 to 4 key messages, followed by detailed topic information and links to other websites for additional evidence-based information. Each fact sheet is supported by an interactive component that enables the user to populate a checklist item summarized on the platform dashboard (Figure 2). For example, opening a fact sheet about cervical screening will populate the *Check my cervical screening status with my GP* item. Health literacy is tested at the top of each fact sheet with a true or false question, with corresponding information that explains the correct answer.

Healthy lifestyle resources include fact sheets related to weight gain prevention and infographics that are based on Australian adult pregnancy [30] and breastfeeding [42] dietary guidelines and physical activity guidelines [43]. Additional resources include information on how to read food labels, how to estimate food portion sizes, healthy snack and food substitution ideas, and calories consumed using various food choices versus those burned from walking. Behavior change is supported by an interactive goal-setting section that guides the user to develop a personalized goal through action planning, which includes an activity to self-select modifiable health behaviors for improvement (eg, packaged or convenience food consumption, alcohol intake, physical activity, fruit and vegetable intake, and sleep). Areas of relevance are selected and prioritized by each participant (ie, areas are ranked in order of importance). Participants are guided through goal-setting using free text to specify what they would like to achieve identify motivating factors and social support pathways, barriers to behavior change and specific strategies to overcome barriers that are time dependent and identification. An action item to review goals will be automatically added to the digital platform, which is encouraged 2 weeks after goal planning and commitment (Figure 2). 

The platform was consumer-tested using a quantitative survey for functionality (ie, ease of navigation across the platform), acceptability (ie, usefulness of the information, presentation and aesthetics, ease of understanding content) and relevance (ie, appropriateness of information, potential for the platform to assist in optimizing health behaviors, peer recommendation). The survey contained a series of statements requiring response on a 5-point Likert scale that ranged from strongly disagree to strongly agree, with an opportunity to provide free text. Responses were transformed to a binary representation (0, disagree and neutral; 1, agree). Overall, 36 women were recruited from the community with advertisements across all modules using both computer (19/36, 53%) and mobile phone or tablet (17/36, 47%) devices. Women were aged between 25 and 38 years old, and the majority were university educated (33/36, 92%). Most women agreed that they could navigate to different areas of the platform and return to the dashboard with ease (23/30, 77%); they found the platform to be aesthetically appealing (25/36, 69%), and the amount of information to be appropriate (28/36, 78%) and easy to understand in its presentation (29/30, 97%). The majority believed that the information would assist them in improving their health-related behaviors (25/30, 83%) and considered the platform relevant to recommend to women of the same life stage (24/36, 67%).

**Figure 2 figure2:**
[figure not shown]
Platform user dashboard.

#### Health Coaching Sessions

Health coaches with a tertiary qualification in health sciences (ie, dietetics, nutrition, exercise physiology, or allied health) will deliver the program and aim for continuity wherever possible to maintain rapport. The purpose of the individual health coaching sessions is to build rapport with participants, reiterate program objectives, enhance engagement, practice goal setting and self-management skills, support participants with lifestyle modules, and provide personalized feedback on behavior change. Any module components that have not been accessed or completed by participants at the point of health coaching will be flagged for completion by the participant during or after the session.

All participants will be offered 2 personalized preconception health coaching sessions (approximately 20 minutes in duration, delivered either be phone or videoconference according to randomization) 2 to 4 weeks after program entry and 6 weeks later.

During pregnancy, 2 additional 20-minute health coaching sessions will be scheduled (8-10 weeks gestation or 1-2 weeks after starting the pregnancy module commencement and 19-20 weeks gestation).

#### Ongoing Program Support

SMS text messages will be sent every 3 weeks as a reminder to practice healthy behaviors.

### Fidelity

Intervention fidelity will be maintained by facilitators using a checklist after health coaching sessions to reduce potential reporting bias. The checklist will include planned discussion points, deviation in delivery of session with reasons, and duration of session. Coaching sessions will be periodically recorded with participant consent to monitor fidelity.

Intervention facilitators will complete program-specific training on the intervention, including health coaching delivery. Facilitators will be required to have a sound knowledge of evidence-based practice; an understanding of health behaviors, nutrition, and physical activity; and a tertiary qualification in a health-related discipline. Program-specific training includes both theory and practical components and motivational interviewing techniques [20-23,44].

### Outcome Measures

Outcome measures (Table 1) are underpinned by the RE-AIM (Reach, Effectiveness, Adoption, Implementation and Maintenance [45]). Both quantitative (recruitment and intervention delivery fidelity checklists [46]) and qualitative (semistructured interviews) data collection methods will be used (Multimedia Appendix 1 and Multimedia Appendix 2).

**Table 1 table1:** Description of outcome measures.

Outcome			Description
**Implementation feasibility (primary)**			Program evaluation and feasibility for future scale up
	Reach	Proportion of the target population that were invited and participated in the program and intervening factors	
	Implementation fidelity	Delivery according to design and any variation experienced Facilitators and barriers: identification and description of intervening events	
	Adoption of the program by the implementation partner	Contextual events or factors influencing implementation within the setting, variation in any co-design implementation component	
	Cost-effectiveness	To answer questions about overall feasibility of implementation	
**Intervention effectiveness (secondary)**			Exploratory evaluation of the effectiveness of intervention delivery across preconception and pregnancy (Figure 1)
	Participation	Adherence and engagement measures to intervention dose including health coaching sessions and web-based platform interaction including degree of module completion, frequency and duration of time spent on the platform	
	Acceptability	A set of questions relating to the influence of the program in changing health behaviors, the usefulness and relevancy of the information provided, valuable aspects of the program and areas for improvement Qualitative data analysis of insights, participation factors, intervention reach, adoption and maintenance of behavior change, intervention delivery format, and areas for improvement until thematic data saturation	
	Effectiveness	On individual health behaviors including self-reported weight, health literacy [47], self-management [48], diet [49], and physical activity [50] using validated questionnaires Collected at the start of the intervention, after preconception health coaching sessions and module, and at the start of the pregnancy module	
	Pregnancy and birthing outcomes	In vitro fertilization utilization (restricted to only hospital component visibility of this process such as retrievals and transfers); gestational diabetes diagnosis, delivery type (ie, vaginal or cesarean section), birth complications and neonatal intensive care unit admission, length and cost of hospital stay and ancillary utilization (ie, physiotherapy, dieticians, dental) Captured via encrypted data linkage with Medibank Private for health outcomes up to and including 5 years after the start of the study as observational study phase data	

### Statistical Analysis

Deidentified quantitative and qualitative databases will be maintained on encrypted Monash University servers and managed by research staff involved in data collection. We will use descriptive approaches to evaluate primary outcomes measures. Quantitative data collected for secondary outcome measures will be exported to STATA (version 17.0; StataCorp LLC). Descriptive statistics (means with standard deviations or frequencies with ranges) will be used to characterize intervention effectiveness and the recruited sample by demographic characteristics (age, BMI, country of birth, education, socioeconomic status, and parity), preexisting health, and health-related behaviors (ie, self-management, diet, and physical activity). Logistic and linear regression models will be used to explore associations between before and after the intervention. Additionally, factors known to influence secondary outcomes, including weight, such as diet, physical activity, breastfeeding status, and parity will be adjusted for a priori. Mixed-effects regression models, with the individual specified as the random effect, will be investigated to account for repeated measures. Missing data will be examined, and multiple imputation will be used to generate complete data, if data are not found to be missing at random. Sensitivity analyses will be performed to explore robustness. A *P* value <.05 will be considered statistically significant.

Transcripts of semistructured interviews will be independently analyzed and coded by 2 researchers using NVivo software (version 12; QSR International). Data will be searched for concepts in relation to participatory factors and program evaluation, with codes generated and grouped into themes using an inductive approach. Quantitative data will be analyzed first, to inform thematic analyses. The definitions of themes will be determined by consensus (between 2 researchers).

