### Hypotheses

We hypothesize as follows:

The intervention will be feasible to implement and can effectively reach and engage women prior to pregnancy through co-designed strategies that are acceptable to women and the implementation partner with demonstrated cost-effectiveness.Participation and engagement with intervention resources will be greater for participants who complete the intended intervention dose compared with those who do not.The intervention will improve preconception and pregnancy health knowledge and self-management.Phone and videoconference health coaching delivery will be equally feasible and cost-effective, yet engagement, adherence, and effectiveness will be greater with videoconference compared with phone-based health coaching.

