## Methods

### Implementation

#### Design

OptimalMe is a type 3 hybrid effectiveness-implementation study [35] with an active intervention phase (2 years) and a passive observation phase (up to 5 years). Type 3 hybrid implementation designs are those in which implementation outcomes are primary, and individual or population outcomes are secondary [35]. The primary outcome of the project includes overall intervention penetration and reach and the feasibility, acceptability, adoption, and fidelity of the delivery of OptimalMe. Secondary outcomes include evaluation of individual health outcomes associated with implementation delivery mode, including knowledge, risk perception, health literacy, self-management, and health behaviors. The study design is a parallel, two-arm, randomized trial at the level of the individual utilizing a pragmatic philosophy, working within real-world conditions to assess overall effectiveness. All individuals will receive the same evidence-based lifestyle intervention, and implementation delivery methods will be compared.

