#### Economic Evaluation

The economic evaluation will be designed to identify the costs associated with implementation, and the net costs to health care funders. Costs of the OptimalMe implementation package will be identified from the trial data, including the costs of platform maintenance, staff time (in providing the coaching sessions), and SMS text messages. Fixed and variable costs will be identified, allowing cost per woman to be estimated at different scales of the intervention. The net costs to health care funders will be identified by quantifying the costs associated with birth type, birth complications, neonatal intensive care unit admissions, hospital stay, and ancillary utilization. Costs to Medicare Benefits Schedule will be identified based upon item numbers [51] associated with birth type and complications. Costs to private health insurers associated with hospital stay will be identified directly from the study. Costs to public hospital funders from neonatal intensive care unit admissions or any public hospital transfers will be identified from the National Hospital Cost Data Collection produced by the Independent Hospital Pricing Authority [52]. The total cost per woman will be calculated, and generalized linear models will be utilized to identify differences in costs between delivery methods. We will use these models to estimate the net cost impacts to different funders at different levels of the population reached.

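### The analysis stated for the secondary outcomes is before versus after and names no delivery-mode term, so the randomised telephone-versus-video contrast has a specified model only for costs

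*Protocol article*

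**What the plan says.** The randomised factor is the mode of coaching, telephone or videoconference (protocol article, Randomization). The first Design section, under Implementation, states: "All individuals will receive the same evidence-based lifestyle intervention, and implementation delivery methods will be compared". The same section defines the secondary outcomes as individual health outcomes tied to delivery mode, and the Framework section also announces a comparison of the two modes. Objective 4 asks whether results differ by mode. Hypothesis 4 reads: "Phone and videoconference health coaching delivery will be equally feasible and cost-effective, yet engagement, adherence, and effectiveness will be greater with videoconference". Hypothesis 3 expects the intervention itself to improve health knowledge and self-management.

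The Statistical Analysis section then sets out the following:
- Primary outcomes: "We will use descriptive approaches to evaluate primary outcomes measures".
- Secondary outcomes: descriptive statistics, and "Logistic and linear regression models will be used to explore associations between before and after the intervention", adjusted for factors such as diet, physical activity, breastfeeding status and parity.
- Repeated measures: "Mixed-effects regression models, with the individual specified as the random effect, will be investigated to account for repeated measures".
- Decision rule: a P "value <.05 will be considered statistically significant".

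Allocation is not mentioned in that section. Under Economic Evaluation, "generalized linear models will be utilized to identify differences in costs between delivery methods".

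**The concern.** The article does fix a contrast for the secondary outcomes, but it is not the one that randomisation protects. Randomisation makes the two coaching groups comparable. It does nothing for a comparison of the same women at two times. A team following this section literally would report change over time in all women together, and would have no specified estimate with which to judge whether video gives greater engagement, adherence or effectiveness.

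The before-after change has its own problem. Women opt in, are planning a pregnancy, and all receive the programme. Some would probably change their diet, activity or knowledge in this period without OptimalMe, and the design has no group that shows how much. Hypothesis 3 is worded as an effect of the intervention, which this contrast cannot establish.

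A smaller point concerns the equality half of hypothesis 4. No margin is given for what counts as equal, and the cost model is aimed at finding differences. A cost difference that fails to reach significance would not show that the modes cost the same.

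**Working it through.** **1. Question against stated analysis.**

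| Question | Where it is asked | Contrast it needs | What the analysis text specifies |
|---|---|---|---|
| Video better on engagement, adherence, effectiveness | Objective 4, hypothesis 4, Design | Video minus phone | Before versus after; no arm term |
| Intervention improves knowledge and self-management | Hypothesis 3 | Programme versus no programme | Before versus after; no untreated group |
| Modes equally feasible | Hypothesis 4 | Phone versus video, with a stated idea of equal | Descriptive; no margin |
| Modes equally cost-effective | Hypothesis 4 | Phone versus video, with a stated idea of equal | Generalized linear model by delivery method, for differences in cost; no margin |

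Only the last row has a model containing delivery mode. The mixed model in the Statistical Analysis section has a random effect for the woman, but neither an arm effect nor an arm-by-time effect is named.

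**2. The plan's own figure.** The Sample Size section gives about 300 women, set by funding, as roughly 10% of eligible women intending to conceive. From the Setting section: 7800 × 0.41 = 3198, and 300/3198 = 9.4%, which agrees with that rounding. No power calculation or effect size is stated, so there is none to reproduce.

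**3. How precisely could the missing contrast be estimated?** Assumptions that are not in the document: 1:1 allocation, 150 per arm, no dropout, and the proportions shown.

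For a difference in proportions, 95% CI half-width = 1.96 × √(2p(1−p)/150):
- p = 0.5: 1.96 × √(0.50/150) = 1.96 × 0.0577 = 11.3 points
- p = 0.7: 1.96 × √(0.42/150) = 1.96 × 0.0529 = 10.4 points
- p = 0.8: 1.96 × √(0.32/150) = 1.96 × 0.0462 = 9.1 points
- p = 0.9: 1.96 × √(0.18/150) = 1.96 × 0.0346 = 6.8 points

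For a continuous score without baseline adjustment: 1.96 × √(2/150) = 1.96 × 0.1155 = 0.23 SD.

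Dropout would widen all of these. The contrast is therefore worth estimating, but around the middle of the range an interval centred on zero would still include differences of 9 to 11 points. That is why a lack of significance should not be read as equality on any outcome.

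**The case against.** The strongest reply is that this is a condensed article. The comparison of modes is announced in the abstract, the objectives, the Design section and the Framework section. Analysts are to be blinded to allocation, which suggests that data will be handled by arm. Model terms are often left to an analysis plan that is not shown here. This stands to the extent that a reader might infer that the arms will never be compared, and the document does not support that. It supports only that no between-arm estimate is specified outside costs. Brevity does not remove the mismatch, however: the section names a contrast, adjusters and a random effect for the secondary outcomes, and the authors did name delivery method when they wrote the cost model.

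Two further inferences are tempting and should not be drawn:
- **That P<.05 will be used to declare the modes equally feasible.** Feasibility is a primary outcome and primary outcomes are to be described, so the document does not apply the threshold to it. What remains is that the word equal has no stated meaning.
- **That the standard errors for change will be wrong because paired records are treated as independent.** A mixed model with the woman as random effect is named for repeated measures, and the regression sentence can also be read as one record per woman. The error is not shown.

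It is also fair to say that Table 1 calls the effectiveness evaluation exploratory, that the sample was not powered on a clinical outcome, and that the absence of an untreated arm is disclosed. These points lower the stakes. They do not make a before-after contrast answer a between-arm hypothesis, or turn uncontrolled change into an intervention effect.

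**Conclusion.** The point holds in this form: the specified regression for the secondary outcomes does not match the randomised question, and the superiority half of hypothesis 4 has no specified between-arm estimate. Hypothesis 3 claims more than an uncontrolled change can support, and a fuller analysis plan could not cure that without rewording the claim. The conclusion rests on the article's wording alone and needs no numerical assumption. Only the precision figures, about 9 to 11 points for proportions between 80% and 50%, depend on the assumed 150 per arm without dropout. The descriptive primary analysis is not affected. I would rate this as should-fix.

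**What to change.** In the Statistical Analysis section, state as the main secondary analysis the video-minus-phone difference with a 95% CI, with women analysed in the mode to which they were randomised:
- **Repeated questionnaire outcomes:** either a mixed model with every time point, baseline included, as an outcome and an arm-by-time term, or post-baseline values only with the baseline value as covariate. Choose one; combining them uses baseline twice.
- **Participation and engagement** (sessions attended, module completion, platform use): a between-arm regression suited to counts or proportions.

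Keep the before-after analysis, but label it as uncontrolled within-woman change, and reword hypothesis 3 to match. Reword the equality half of hypothesis 4 as estimation of the difference in feasibility and cost-effectiveness with CIs, since no margin is stated.

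The cost is a change of wording in the analysis section and in two hypotheses, with no extra data. The downside is a weaker claim about the overall effectiveness of the programme.

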#### Setting

The Australian health care system is government supported via Medicare, which provides universal free care to Australian citizens and residents (and others who are eligible) and is supported by a subsidized private health system. Private health insurance, paid by the individual, allows patients to choose hospitals and health care providers from outside of the public system, with a 12-month waiting period before some, or all, of the cost of hospital treatment is reimbursed. Overall, approximately 54% of Australian adults have a form of private health insurance [36], and 27% of births in Australia occur in private hospitals [37]. Women who give birth in private hospitals attend ambulatory private obstetric care and have limited contact with hospitals prior to delivery.

Women who upgrade private insurance to include, or join with, pregnancy and birth coverage, comprise a unique population, prospectively signaling future intention for a pregnancy. In a sample of 294 women who had recently upgraded or obtained insurance for pregnancy and birth coverage, 41% intended to conceive within the next 12 months [33].

The implementation partner in this research program is Medibank Private, which is one of Australia’s largest insurers (funding approximately 20,000 births annually). Feasibility scoping shows approximately 7800 women join with, or upgrade to, pregnancy and birth coverage with this insurer nationally each year.

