#### Sample Size

Given the implementation effectiveness study design, sample size has not been powered on a clinical outcome because the primary outcome is to determine implementation learnings to inform feasibility. Available funding enables intervention delivery to approximately 300 women, which is approximately 10% of the eligible population with intention to conceive, based on our formative research [33].

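### The trigger for multiple imputation is the wrong way round: it is tied to data that are not missing at random, the case in which standard imputation is generally biased

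*Protocol article*

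**What the plan says.** The rule is in the Statistical Analysis section of the protocol article. Missing data are to be examined first, and then "multiple imputation will be used to generate complete data, if data are not found to be missing at random". No other section gives a different rule.

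The surrounding text determines what the rule acts on:

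- Before-after comparison: "Logistic and linear regression models will be used to explore associations between before and after the intervention".
- Repeated measures: "Mixed-effects regression models, with the individual specified as the random effect, will be investigated to account for repeated measures".
- Robustness: "Sensitivity analyses will be performed to explore robustness". No method for data missing not at random is named.
- Primary outcomes: "We will use descriptive approaches to evaluate primary outcomes measures".

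Table 1 lists self-reported weight, health literacy, self-management, diet and physical activity as secondary effectiveness measures. They are collected at the start, after preconception coaching, and at the start of the pregnancy module. The table calls this evaluation exploratory.

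**The concern.** MI as normally implemented fills in values from a model fitted to the observed data. It is justified when, given the variables in that model, missingness does not depend on the unseen values. That is the MAR assumption. The article makes the failure of that assumption the condition for imputing, and gives no condition for imputing when it holds.

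The questionnaire outcomes and self-reported weight depend on women returning follow-up data in an opt-in, low-intensity programme. The second hypothesis already expects some women not to complete the intended dose, so loss related to engagement or starting behaviour is plausible. These outcomes carry the third objective (individual health effects) and part of the fourth (differences by coaching mode). At stake are the before-after estimates for these measures and, under conditions set out below, the comparison of telephone with videoconference.

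**Working it through.** The article states no figure for missing data, so there is none to reproduce. The check is one of logic, followed by an illustration.

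**1. The rule against the assumption behind MI**

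| Data are | Rule as written | Standard MI |
|---|---|---|
| MAR | no imputation called for | valid |
| MNAR | impute | generally biased |

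The two columns are opposed in both rows.

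**2. Can the trigger be operated?** Let R mark a missing follow-up, Y0 the baseline and Y1 the follow-up. MAR requires P(R | Y0, Y1) = P(R | Y0). Checking this needs Y1 for the women in whom it is missing. What the data can show is whether R is related to Y0, which bears on missing *completely* at random and not on MAR against MNAR.

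**3. Illustration.** All inputs except n are assumed, because the documents give none:

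- n = 300 (the recruitment target), 2,000 simulated trials, 20 imputations each
- Y0 ~ N(0, 1); Y1 = 0.3 + 0.6·Y0 + 0.8·e with e ~ N(0, 1), so the true mean change is 0.30 SD and the correlation 0.6
- log-odds of missing follow-up: −0.95 (MCAR), −0.95 + Y0 (MAR), −0.95 + Y1 (MNAR)

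| Mechanism | Missing | Paired completers | MI | Likelihood (mixed-model type) |
|---|---|---|---|---|
| MCAR | 28% | 0.300 | 0.300 | 0.299 |
| MAR | 31% | 0.406 | 0.302 | 0.302 |
| MNAR | 37% | 0.177 | 0.091 | 0.091 |

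The MAR row can be followed by hand. Completer change = 0.3 + (0.6 − 1) × mean Y0 among completers. Setting this to 0.406 gives a mean Y0 of (0.406 − 0.300)/(−0.4) = −0.265: completers started lower than the full sample, and the paired change absorbs that.

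**4. Does the direction hold?** No. Now let lower scorers be the ones who drop out, with correlation 0.5–0.7, 30–40% missing and a log-odds slope of 0.5–1.0 per SD. Under MAR, paired completers give 0.13–0.26 and MI gives 0.30. Under MNAR, MI gives 0.37–0.56. Both biases change sign. What does not change is that MI recovers the truth under MAR and misses it under MNAR.

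**5. Between-arm contrast.** With the same ranges, a second arm and a true difference of 0.20 SD, and drop-out depending on baseline only (MAR), completers give:

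- regression adjusted for baseline: 0.198–0.202, even when the drop-out slope differs by arm
- unadjusted, common slope: 0.197–0.202
- unadjusted, slope differing by arm: 0.02–0.14 in the configuration run; the direction depends on which arm has the steeper slope

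Under MNAR with a mechanism common to both arms, the adjusted contrast was 0.17–0.20.

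**The case against.** The strongest defence is that the authors meant *not missing completely at random*. That would be a common trigger, and one the data can inform. It may well be what was intended, but it is an inference; an analyst following the text would impute in the wrong case.

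Second, the mixed-effects models in the same section would be valid under MAR without imputation if fitted by likelihood to all available data (0.302 against 0.30 above). This is real mitigation. It is incomplete because those models are only to be investigated, while the linear and logistic regressions are definitely to be used.

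Third, an article may leave imputation details to a fuller plan. That is right for the imputation model and its auxiliary variables, and their absence is no fault here. The trigger is different: it is stated, and stated wrongly.

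Fourth, a reader might infer that every individual-level result is exposed, or that before-after and between-arm estimates are biased whichever branch applies. The documents do not support either. Table 1 takes pregnancy and birth outcomes from insurer data linkage and participation from coaching sessions and platform interaction. A baseline-adjusted contrast in completers can be unbiased under MAR, as step 5 shows; the article does not say whether the baseline value is a covariate, so that protection is possible but not assured. The sentence also does not say that MI is used *only* in the stated case, although it offers no other.

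**Conclusion.** The rule is wrong as written and should be corrected. The reversal and the impossibility of identifying MAR or MNAR from observed data rest on no numerical assumption.

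The consequence is limited. Before-after change in the questionnaire outcomes and self-reported weight can be biased under MAR if the analysis rests on completers. Between-arm contrasts can be biased under MAR if they are not adjusted for the baseline value and drop-out differs by arm. The MNAR case is presented as handled when it is not. Size and direction cannot be derived from the documents: the simulated values depend on assumed correlation, effect and drop-out, and the sign reverses with who drops out.

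It would be tempting to read this as a threat to the trial's main conclusions. It is not. Implementation outcomes are primary and analysed descriptively, and the affected outcomes are secondary and labelled exploratory. This is an inexpensive correction to secondary analyses.

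**What to change.** Delete the condition that makes MI depend on what is found about the missingness mechanism, and replace the sentence with wording such as:

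> The main analysis of secondary outcomes assumes that data are missing at random and uses either a likelihood-based mixed model on all available data or multiple imputation that includes the baseline outcome. Sensitivity analyses will include departures from this assumption, for example by delta-adjusted imputation.

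The mixed model is already contemplated in the Statistical Analysis section, and the sensitivity analyses are already promised there; the change commits to a main method and gives the second a defined purpose. Further imputation detail can stay in a fuller analysis plan.

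Cost: one or two sentences and a little more analysis time. No new data are needed.
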